#### Data Collection, Management, and Monitoring

Data will be collected via a web-based data collection tool (*LimeSurvey*; LimeSurvey GmbH [31]), provided by the study sponsor’s affiliated university. Participants will be allowed to skip questions if they experience discomfort. At the end of each survey, the participants may enter feedback or additional comments into a text box. Participants will receive reminder emails prompting them to complete the surveys. Data from randomized noncompleters will be used to calculate the loss to follow-up rates.

Data management will take place at the site of the study sponsor. The research team members will be responsible for data entry, coding, security, and storage. Range checks for data values will be conducted, and additional steps will be taken to ensure data quality; data checks will be performed by 2 research team members who will also double check whether the coding has been performed correctly. Data will be stored on a safe university-based network location that will only be accessed by authorized research staff.

The data monitoring committee will comprise the team members of the study sponsor. There will be a regular correspondence between the data collection site and the principal investigator to ensure adherence to the protocol, which has been approved by the university-based institutional review board (IRB). The study funder will reserve the right to terminate the study at any point. Adverse events will be reported to the IRB. Documentation of such events will be stored on the university’s safe network location. No interim analyses are planned.

#### Outcomes

The German version of each questionnaire has been previously validated. All outcomes of interest consist of continuous variables based on self-report data. Our primary outcome will be perceived stress measured using the 10-item Perceived Stress Scale (PSS-10) [32]. Secondary outcomes will include sense of happiness (Likert scale) [33], life satisfaction (L-1) [34], mindfulness (Five Facet Mindfulness Questionnaire) [35], well-being (World Health Organization-Five Well-Being Index) [36], self-care (Hamburg Self-Care Questionnaire; only pacing scale) [37], pain intensity (numerical rating scale 0-10) [38], work-related sense of coherence questionnaire [39], burnout (Copenhagen Burnout Inventory; work-related burnout scale and client-related burnout scale) [40], job satisfaction (Warr-Cook-Wall Scale [41], modified by Cooper et al [42]), and work engagement (Utrecht Work Engagement Scale) [43].

#### Other Variables

##### Participants’ Characteristics

Sociodemographic variables will include age (in years), gender (male, female, or diverse), relationship status (categorical variable), children (yes or no), previous meditation experience (yes or no), and participation in other studies to promote health (yes or no).

We will assess for job-related variables. We will assess participants’ job status (nurse or nursing trainee) and work status (part-time or full-time); if part-time, we will assess the number of work hours per week (per employment contract), number of hours worked per week during the past 4 weeks (including overtime), patient contact during the past 4 weeks (scale 0%-100%), current area of care (eg, internal medicine, surgery, multiple possible answers), duration of employment at the current workplace (in years), job-related tasks that involve caring for patients with COVID-19 more than half of the time (yes or no), working in a hospital with incentives for study participation at T0 (yes or no), and employer permission to participate in study activities during work hours (yes or no). We will assess the following job-related variables for only nurses: qualifications beyond training (eg, additional qualifications, bachelor’s degree, or master’s degree) and years of work experience. We will assess the following job-related variables for nursing trainees only: focus of training (general nursing, pediatric nursing, or care of older adults) and year of training.

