#### Study Setting

This study will be conducted at 4 hospitals and hospital-associated nursing schools in North Rhine-Westphalia, Germany. The number of nurses employed at each institution ranges from 40 to 1400. Two of the hospitals are acute care hospitals with emergency departments, whereas the other 2 hospitals specialize in pneumonology and cardiac surgery. The 2 nursing schools currently have a total of 280 and 380 enrolled nursing trainees.

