#### Recruitment

Recruitment took place between August and October 2021 during hospital staff meetings, as well as during web-based meetings among project partners, which were attended by nurses. In addition, participants were recruited via weekly newsletters, handbills, and flyers handed out at participating hospitals and nursing schools.

Eligible nurses and nursing trainees interested in participating in the study were able to register via a website and were emailed the link to the time point 0 (T0) survey (baseline survey). Upon obtaining informed consent, participants were prompted to fill out the web-based survey. Information regarding the study design was not disclosed to the participants.

Informed consent was obtained from all participants before the start of each web-based survey. Informed consent materials are currently available only in German (Multimedia Appendix 1). To prevent individuals from participating more than once, we checked for duplicates in the first and last names and email addresses during registration. Each registered person received personalized invitation letters via email with an individual access key to the survey (token).

Incentives for study registration and survey participation were available at the discretion of each hospital’s management, thus varying across locations. A raffle was initiated by the intervention provider at one of the hospitals to incentivize staff participation in the surveys. Incentives included 15 gift cards €15 (US $15.8) each for various shopping websites for the first 2 surveys, whereas the last survey was incentivized by the opportunity to win 1 of the 10 gift cards €30 (US $31.6) each. At some participating hospitals, participants were allowed to participate during work hours, whereas others required their staff to partake during their personal time.

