Using the pooled data set, to determine which variables are associated with adherence at 10 weeks and 24 weeks after intervention start, we will examine the correlations between the variable *frequency of meditation practice* and participants’ baseline characteristics, acceptability, and intensity of intervention use using the ITT sample. To assess adherence at 38 weeks after the intervention, analyses will be conducted using the ITT data set of the IG.

##### Research Question 4

Using the pooled data set, to determine which variables are associated with acceptability at 10 weeks after the intervention start and 24 weeks after the intervention start, we will examine the correlations between the variable of *perceived usefulness* (acceptability) and participants’ baseline characteristics and intensity of intervention use using ITT sample. To assess acceptability at 38 weeks after the intervention, analyses will be conducted using the ITT data set of the IG.

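### Incentives and work-time permission follow the hospital, so person-level correlations with adherence and acceptability cannot separate them from hospital and give P values that are too small whenever hospitals differ

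*Protocol article*

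**What the plan says.** Under Study Setting: "This study will be conducted at 4 hospitals and hospital-associated nursing schools in North Rhine-Westphalia, Germany". The same section gives nursing staffs of 40 to 1400; two hospitals are acute care hospitals with emergency departments and two are specialised.

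Under Recruitment, incentives were left to each hospital's "management, thus varying across locations". It adds: "A raffle was initiated by the intervention provider at one of the hospitals to incentivize staff participation in the surveys". On work time: "At some participating hospitals, participants were allowed to participate during work hours, whereas others required their staff to partake during their personal time".

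Under Participants' Characteristics, both matters become items recorded for each participant. The incentive item reads "working in a hospital with incentives for study participation at T0 (yes or no". The item on work time is likewise a yes/no answer for each person, worded as "employer permission to participate in study activities during work hours (yes or no".

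The Overview of Statistical Methods assigns Pearson correlation, eta and chi-square tests to research questions 3 and 4. Research Question 3 relates meditation frequency to "baseline characteristics, acceptability, and intensity of intervention use using the ITT sample". Research Question 4 relates perceived usefulness to baseline characteristics and intensity of use. Neither section states a hospital term or any allowance for clustering. The Overview also says that P values outside the primary outcome will be read descriptively.

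**The concern.** The incentive item asks about the hospital, so by its own wording everyone at one hospital has the same value. Permission is answered by each person, but Recruitment describes it as differing between hospitals. The tests named treat every participant as independent information on both items.

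Two problems follow. First, confounding: a variable that is constant within four hospitals cannot be separated from size, specialty, workload or anything else that differs between them, and recruiting more people at the same hospitals would not help. Second, precision: the standard error is based on the number of people, although the contrast is between hospitals.

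Adherence and acceptability are two of the four stated research questions, and the Abstract expects these findings to inform decisions on implementation. A hospital difference could be published as an association with incentives or protected time, with more apparent support than the design can give.

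**Working it through.** **The plan's own figures.** The article gives no figure for these correlations. Its only calculation is for the primary comparison: 36 per group at d = 0.67, two-sided 5%, 80% power. This reproduces (power 0.8005 at 36 per group; 72/0.80 = 90 after 20% dropout) and has no bearing on this point.

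**Inputs from the article.** Four hospitals (Study Setting); 79 people randomized, 40 and 39 (Results); 20% dropout assumed (Sample Size), so 0.80 × 79 ≈ 63.

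**Assumptions.** The article gives neither the number of participants per hospital nor the intracluster correlation (ICC, the share of outcome variance lying between hospitals). Both are varied below.

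**Variance inflation.** For a yes/no variable constant within about equal hospitals of m people, the variance of the difference in means is larger than the person-level test assumes by the factor 1 + (m − 1) × ICC. With m = 20 and ICC = 0.05 this is 1 + 19 × 0.05 = 1.95. The actual false-positive rate of the nominal 5% test is then roughly P(|Z| > 1.96/√1.95) = P(|Z| > 1.40) ≈ 16%.

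**Simulation.** 20,000 data sets per setting, no true association, hospitals of 20/20/20/19, one hospital exposed, two-group t test (equivalent to the Pearson test of a yes/no variable):

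| Assumed ICC | Variance inflation | False-positive rate at nominal 5% |
|---|---|---|
| 0 | 1.00 | 5.0% |
| 0.01 | 1.19 | 7% |
| 0.02 | 1.38 | 9% |
| 0.05 | 1.95 | 16% |
| 0.10 | 2.89 | 25% |
| 0.20 | 4.78 | 39% |

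Two exposed hospitals against two give nearly the same rates.

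**Sensitivity to the other assumptions.**
- With 63 people in equal hospitals, the rate is about 14% at ICC 0.05 and 22% at 0.10.
- With unequal hospitals of 40/20/12/7 and ICC 0.05, it is 20% if only the largest is exposed and 10% if only the smallest is.
- At 38 weeks only the intervention group is analysed. With 40 people, m = 10 and ICC 0.05, the inflation is 1 + 9 × 0.05 = 1.45, and P(|Z| > 1.96/√1.45) = P(|Z| > 1.63) ≈ 10%.

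The simulation uses a continuous outcome; the chi-square version was not simulated.

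**With the hospital as the unit.** Four hospital means leave 4 − 2 = 2 degrees of freedom, so the critical t is 4.30 instead of 1.99 (77 degrees of freedom). Permuting hospitals, the smallest possible P value is 1/4 = 0.25 for one against three and 2/6 = 0.33 (two-sided) for two against two. No hospital-level test could reach 5% by permutation, whatever the data.

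**The case against.** The strongest reply is that the plan claims little here. Its research questions ask which variables are associated with adherence and acceptability, and the Overview calls everything outside the primary outcome exploratory, with P values read descriptively. A false-positive rate measures a 5% decision rule that the plan does not apply to these tests. That stands against any reading that a confirmatory conclusion is at risk. It does not remove the point: the exploratory label is given as a guard against multiplicity, and it cures neither the confounding nor a standard error computed on the wrong unit. A descriptive P value still misleads if it is too small.

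Other parts of the reply also stand:
- The inflation depends on an ICC that the article does not give; at 0 to 0.01 it is negligible or slight.
- The one-hospital fact concerns the raffle. The number of hospitals offering any incentive at T0 is not stated, so a one-against-three split for the incentive item is not established.
- Permission is recorded per person, and nothing says that answers are constant within a hospital.
- The incentives were for registering and completing surveys, not for meditating, so it is not established that these two items would be the findings acted on.

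It can also be said that a full analysis plan may settle the list of variables, and that the Overview promises alternative tests if assumptions fail. But the article itself names these items as characteristics and names the tests, and an alternative person-level test would leave the confounding in place.

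**Conclusion.** The point holds in a limited form. For the incentive item, and for permission as far as it follows the hospital, the planned person-level tests cannot separate policy from hospital, and their P values are too small whenever hospitals differ. With 79 people in four about equal hospitals, a nominal 5% becomes about 9%, 16% and 25% at ICC 0.02, 0.05 and 0.10, and stays at 5% at ICC 0. ICC and hospital sizes are assumptions. The confounding does not depend on them.

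A reader might infer more: that the trial will report an effect of incentives or permission, that the P values are far too small whatever the ICC, or that the main result is compromised. The article supports none of these. It plans associations only, the ICC is unknown, and research question 1 compares individually randomized groups stratified by hospital.

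**What to change.** Take the incentive item out of the correlation and chi-square tests for research questions 3 and 4. Do the same for work-time permission unless answers vary within hospitals; if they do, use only that within-hospital variation. In place of these tests, add one table with a row per hospital showing its incentive policy, its work-time policy, and descriptive summaries of meditation frequency and perceived usefulness. State beside it that these policies cannot be separated from other differences between the hospitals.

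Adjusting the remaining participant-level associations for hospital (4 − 1 = 3 degrees of freedom) is an optional sensitivity check. The calculations above cover only variables constant within hospitals and do not show that the others need it.

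The cost is some wording and one table; no new data are needed. The downside is that there is no P value for the incentive item, nor for permission unless it varies within hospitals.

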##### Adherence

Adherence to the instructions for using the digitally supported mindfulness intervention will be operationalized as daily meditation. The frequency of meditation practice (app-based and non–app-based meditation) will be recorded based on the following answer options: several times per day, daily, 4 to 6 times per week, 1 to 3 times per week, less than 1 time per week, or never.

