## Introduction

### Need for Effective Stress Management Interventions for Nurses

The increasing psychological and physical burdens and high workloads of nurses and nursing trainees worldwide have been raising concerns for some time [1,2]. Nurses and nursing trainees in acute inpatient care settings are disproportionately affected by burnout and mental illnesses. Nursing trainees also experience high stress levels, with 34% reporting depressive symptoms before the COVID-19 pandemic [3]. Working in acute inpatient care settings has grown to be increasingly demanding throughout the pandemic; findings from a meta-analysis revealed that 30% [2] to 43% [1] of nurses experience work-related stress. The stress of health care professionals may diminish the quality of care provided to patients and can negatively affect other system-relevant factors [4-7]. Stressful work conditions may also decrease the willingness of nurses to continue working within their profession, which in turn facilitates nursing staff shortages in several countries [8], including Germany [2].

Currently, knowledge about effective stress management interventions to reduce these global challenges is limited. The available research on the effectiveness of stress management interventions for nurses has limitations, including small sample sizes limiting the validity and generalizability of the results and a lack of long-term follow-up [9-11]. More research is needed to examine which interventions result in positive outcomes and, more importantly, the conditions on which intervention effectiveness depends (eg, care setting and acceptability). Therefore, this study distinguishes between efficacy and effectiveness. Efficacy refers to the observed intervention effect when the protocol is followed, whereas effectiveness refers to the effect observed for the entire sample, regardless of protocol adherence.

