#### Intervention

The intervention will be initiated by email. The email will contain the app access code, workbook pickup location at each hospital, and a list of proposed dates for web-based workshops. Participants will be given instructions on how to download the app from the app store and activate the code. The access code will allow access to the full app version, including meditations and education courses tailored to nurses for a 12-month period (Figure 1 [29]). The intervention will be free of charge for the participants.

The standardized multimodal stress management intervention comprises 3 components (an app, 2 web-based workshops, and a workbook). The web-based workshops and the workbooks are supplemental to daily app-based meditation. In-person interaction will occur only during the web-based workshops when participants will interact with the MBSR trainer and other group members. In case technical difficulties are encountered, information technology support will be available to the participants.

The app contains >900 meditation exercises and educational content on mindfulness and meditation. The app is available in German, French, Dutch, and English. In addition, the app features 3 content areas tailored specifically to nurses, which were developed by researchers in the nursing field (Table 2).

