Participants will be instructed to meditate daily via the app, web-based workshops, and workbook. No standardized prompts or reminders to meditate will be provided, and participants will be able to choose the frequency and duration of their meditation freely. Participants will have the option to choose whether to receive a weekly email newsletter from the intervention provider.

App development started in 2014. Since then, the app has been one of the most frequently downloaded meditation applications in Germany; health insurance companies cover the costs associated with gaining access to specific app-based prevention courses that are otherwise only available via the premium version of the app. There is only one previous peer-reviewed evaluation among office workers indicating significant improvements in mindfulness, work engagement, job satisfaction, emotional exhaustion, emotional intelligence, innovation and creativity, and self-efficacy after using the app for 14 days [30].

No substantial revisions to the app are planned, and the anticipated app updates are limited to minor bug fixes. The present intervention will use the app versions available in the Apple App Store and Google Play Store. No quality assurance methods have been planned to ensure the accuracy and quality of the information provided by the intervention provider.

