##### Intensity of Intervention Use

App use will be measured through previous experience with the app (“yes, I have tried out the app”; “yes, I use the app regularly”; or “no, I have never used the app”), previous experience with the app before code activation (“yes, I have tried out the app”; “yes, I use the app regularly”; or “no, I have never used the app”), date of access code activation (yes [date of activation] or no), total amount of app-based meditation (in minutes), total number of app-based meditation exercises, subjective assessment of app use frequency (several times a day, daily, 4-6 times per week, 1-3 times per week, less than once a week, or never), time of use (in my free time, before my shift, during my shift, during my breaks on shift, or after my shift), and use of the app-based nursing-specific courses (list of nursing-specific courses; selection of multiple answers).

Participation in the 2 user-engaging components (web-based workshop and workbook) will be assessed using a binary variable (yes or no). Frequency of workbook use will be assessed using the following answer options: several times a day, daily, 4 to 6 times per week, 1 to 3 times per week, less than once per week, or never. Finally, we will assess for non–app-based meditation (yes or no).

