#### Statistical Methods

##### Overview

Analyses will be conducted using *SPSS Statistics* (IBM)*.* For tests involving our primary outcome variable, we will set an α level of .05. For all other analyses, to reduce α-error inflation, we will interpret the obtained *P* values descriptively, meaning all other analyses will be exploratory and are designed to observe trends and not to identify significance.

Patterns of missing data will be assessed, and adequate data imputation techniques such as multiple imputation with *SPSS Statistics* (IBM) will be applied. Before doing so, we will assess the percentage of missing data. We will also use Little's Missing Completely At Random test to determine patterns of missing data (ie, missing completely at random vs not missing at random).

We will reverse code 3 outcomes [32,38,40] so that a higher score indicates health improvement. For example, the scale assessing burnout [40] is designed to indicate that a score of 1 indicates a rather minuscule risk of burnout, whereas a score of 100 indicates the highest risk of burnout, meaning that greater scores indicate a worsening of symptoms. After recoding this variable, greater scores will reflect a lower risk of burnout (ie, an improvement in symptoms).

Effectiveness will be evaluated using an intention-to-treat (ITT) approach; all randomized participants will be included in our analyses [45].

Efficacy will be evaluated using a per-protocol (PP) approach; only study completers who report adherence will be included in our analyses.

Several analyses will be used to address the research questions. To ensure that our randomization has worked as intended, we will assess for between-group differences for relevant participant characteristics and, if needed, adjust the following analyses. For research questions 2, 3, and 4, we will create a pooled data set merging the data of the IG and the WCG. We will merge the data of the 2 groups so that IG T0 data will be combined with WCG T1 data, and IG T1 data will be combined with WCG T2 data, as described in Textbox 1. For research questions 3 and 4, relationships between variables will be examined using correlation analyses (Pearson correlation coefficient, eta quotient, and chi-square tests). If violations of the assumptions associated with any of the analyses are detected, alternative tests will be used.

Data pooling procedure.

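### The per-protocol efficacy set can admit a daily meditator who received none of the study intervention

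*Protocol article*

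**What the plan says.** Four parts of the protocol article bear on this.

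- **What efficacy means** (Introduction, Need for Effective Stress Management Interventions for Nurses): "Efficacy refers to the observed intervention effect when the protocol is followed".
- **What the intervention is** (Intervention): "The web-based workshops and the workbooks are supplemental to daily app-based meditation". After Table 2, the same section gives the instruction: "Participants will be instructed to meditate daily via the app, web-based workshops, and workbook".
- **What adherence is** (Other Variables, Adherence): "Adherence to the instructions for using the digitally supported mindfulness intervention will be operationalized as daily meditation". The measurement follows: "The frequency of meditation practice (app-based and non–app-based meditation) will be recorded based on the following answer options". The answers run over six levels, from several times a day to never.
- **Who enters the per-protocol set** (Statistical Methods, Overview): "Efficacy will be evaluated using a per-protocol (PP) approach; only study completers who report adherence will be included in our analyses".

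A separate section, Intensity of Intervention Use, collects access-code activation, app-use frequency on the same six-level scale, app minutes, number of app exercises, workshop and workbook participation, and a yes/no item on non-app meditation. None of these enters the per-protocol definition.

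**The concern.** A per-protocol set is meant to contain people who received the intervention as planned. Here membership depends on meditation of any origin. Previous meditation experience is recorded as a participant characteristic and is not an exclusion criterion, so people with their own practice can be in the trial.

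The per-protocol result carries weight in this plan. Efficacy is named in the objective beside effectiveness. Research Question 1 runs the two-sample t test in both the intention-to-treat and the per-protocol samples, and the Overview sets α at .05 for tests on the primary outcome. The per-protocol result on the PSS-10 would therefore be read as a test. The long-term efficacy analyses and the regression on app minutes in Research Question 2 also use the per-protocol approach.

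If the set contains people with no exposure, the estimate is no longer the effect of following this protocol. The error can go either way. Stable meditators who have little room to change would dilute it. People who improve through an unrelated practice would have that improvement credited to the programme.

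**Working it through.** **Step 1. Apply the rule as written to two intervention-group completers.**

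- *Person A* never activates the code, attends no workshop, uses no workbook, and meditates daily by another method. The frequency answer is daily, so A is adherent and enters the per-protocol set.
- *Person B* uses the app 4 to 6 times a week and does no other meditation. The answer falls below daily, so B is not adherent and is left out.

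A's inclusion follows from counting all meditation without asking about exposure. B's exclusion has a different cause, the daily cut-off.

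**Step 2. Check whether another reading removes the problem.**

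- If the parenthesis in the Adherence section described two items, adherence would still be daily meditation, with no restriction to study content.
- Research Question 3 treats adherence as one variable, the frequency of practice, and correlates it with intensity of intervention use. App use is thus handled as a separate construct.
- Table 1 schedules adherence at T0, before allocation and before any access. An established daily meditator could meet the criterion before the intervention starts.
- Table 1 limits adherence at T1 to the intervention group, so at T1 there is no matching selection on meditation among the controls.

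**Step 3. Size, as an illustration only.** The plan's own figure comes first. Inputs from Sample Size: d = 0.67, two-sided α = .05, power .80. The noncentral t calculation gives 35.96, so 36 per group, with power 0.8005; 36 / (1 − 0.20) = 45 per group. The stated 72 and 90 are reproduced and not disputed.

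The Results section reports 40 and 39 randomized. With the plan's 20% dropout, 40 × 0.8 = 32 and 39 × 0.8 = 31.2, taken as 31. Let f be the share of the intervention-group per-protocol set with no exposure. Assume zero effect in those people, an unchanged SD, and 0.67 in everyone else. Then d in the set = 0.67 × (1 − f). The last column assumes that only half of the 32 completers report adherence.

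| f (assumed) | d | Power, 32 vs 31 | Power, 16 vs 31 |
|---|---|---|---|
| 0 | 0.670 | 0.744 | 0.568 |
| 0.10 | 0.603 | 0.654 | 0.483 |
| 0.25 | 0.503 | 0.501 | 0.359 |
| 0.50 | 0.335 | 0.258 | 0.187 |

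The document gives neither f nor the size of the per-protocol set. The table covers dilution only; bias in the other direction is not quantified.

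**The case against.** The best defence is that non-app practice is partly study content. The programme has three components, the workshops present exercises that do not use the app, and the instruction to participants names the workshops and workbook as well as the app. The Strengths and Limitations section says that the intervention is to be studied as a whole. An adherence item covering both kinds of practice is a reasonable match to that instruction, and a rule based on app use alone would wrongly drop someone who practises workshop exercises daily. This stands, and it shapes the fix. It does not rescue the rule, because the item cannot tell workshop-taught practice from unrelated practice and no exposure is required.

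A second defence is that the plan does use app data: Research Question 2 regresses difference scores on app minutes, and Research Question 3 relates practice to intensity of use. That is true, so it would go too far to say that Research Question 3 describes only meditation in general. But the regression runs under the same per-protocol approach and does not repair the set.

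A reader might also infer that counting non-app meditation pushes consistent app users out. The text does not support this. The daily cut-off excludes them, and counting other practice makes it easier for them to qualify.

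Finally, person A may be rare: a daily meditator who registers, completes the surveys and never uses any component. The document gives no frequency for this, in either direction.

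**Conclusion.** The point holds as a defect of definition. As written, the per-protocol set can include intervention-group completers with no exposure to the programme, which contradicts the article's meaning of efficacy, its account of the core component and its instruction to participants. The conclusion rests on the wording alone.

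Its practical size is unknown. The values in the table depend on an assumed f, on zero effect in the unexposed, and on borrowing a planning effect set for the comparison between groups. A reader might infer a particular degree of attenuation, or that the trial's main comparison is compromised. Neither follows: no share can be derived from the document, and the intention-to-treat analysis includes everyone randomized whatever their practice. The matter should be corrected before analysis, but it does not threaten the trial's effectiveness result.

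**What to change.** In Statistical Methods, Overview, add one condition for intervention recipients in the per-protocol set, on top of the plan's own frequency criterion: recorded exposure to the study intervention. The items under Intensity of Intervention Use suffice, namely code activated with app use reported, or participation in a workshop or the workbook. At T1 the condition applies to the intervention group only; in the pooled data set it applies to both groups after their own start.

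Report a sensitivity per-protocol analysis that uses the app-use frequency item in place of the all-meditation item. Keep all-meditation frequency as a descriptive variable. Reconcile the Adherence section with the Intervention section, which calls app practice the core, instructs daily practice through all three components, and also lets participants choose their own frequency.

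No new data are needed, and the article says that analysis starts only after data collection ends, so the definition can be settled beforehand. The per-protocol set may become slightly smaller. Exposure would still be self-reported, because app use is not tracked.
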